### Control subjects

To potentially replicate and expand findings concerning the neural correlates of tinnitus, 25 control subjects without tinnitus but matched for age, gender and hearing function are examined once using EEG, MRI, functional MRI and all questionnaires (except for the tinnitus-specific ones). Inclusion criteria for the control subjects are age between 18 and 70 years and written informed consent. Exclusion criteria are identical to the exclusion criteria for patients except for the first three criteria.

### Procedures

Patients are recruited during routine clinical tinnitus consultations, via print-media announcement and via the homepage of the multidisciplinary tinnitus clinic at the University of Regensburg. At screening, all patients are asked to fill in the Tinnitus Sample Case History Questionnaire
[23], and inclusion/exclusion criteria are checked. After screening and giving written informed consent, patients are examined in a baseline visit that involves structural MRI, resting state functional MRI and resting state EEG measurements (see Figure 
1). Those measurements are repeated after completion of rTMS treatment. After a 3-month follow-up period, an additional resting state EEG measurement is done. Furthermore, questionnaires have to be filled out at different time points including follow-up visits after 3 and 6 months (see Figure 
1).

**Figure 1 F1:**
[figure not shown]
**Visit schedule.** EEG, electroencephalography; (f)MRI, (functional) magnetic resonance imaging; rTMS, repetitive transcranial magnetic stimulation.

### (Functional) MRI/electroencephalography

The MRI scans are performed on a Siemens Allegra 3-Tesla head scanner (Siemens AG, Erlangen, Germany) with a single channel headcoil. First, a high-resolution T1 weighted image (160 sagittal slices covering the whole brain, 1 × 1 × 1 mm^3^ voxel size, field of view = 256 × 256 mm^2^) is acquired from each subject using the ADNI sequence (repetition time = 2250 ms, echo time = 2.6 ms, flip angle = 9°). Then 6 minutes of resting state functional MRI are performed using a T2* weighted gradient echo-planar imaging sequence (repetition time = 2 seconds, echo time = 30 ms, 34 slices, field of view = 192 × 192 mm^2^, flip angle = 90°, 3 × 3 × 3 mm^3^ voxel size). The EEG equipment consists of the BrainAmp DC amplifier (Brain Products, Herrsching, Germany) and EEG recording caps with the possibility to place up to 64 electrodes (10–20 System; EasyCap, Gilching, Germany). The EEG is recorded from 62 electrodes with impedances below 10 kΩ and a sampling rate of 500 Hz. A resting state EEG measurement is carried out for 7 minutes with eyes closed.

### Questionnaires

To assess tinnitus severity, tinnitus patients have to fill in different tinnitus questionnaires at several time points (see Figure 
1): the THI, the German version of the TQ
[22,24] and numeric rating scales for tinnitus loudness and annoyance. In addition, depressive symptoms, quality of life and hyperacusis are assessed using the Major Depression Inventory, the World Health Organization Quality of Life assessment and a German hyperacusis questionnaire
[25].

### Treatments

On the first treatment day, patients are randomized to one of the following two parallel groups.

The multisite group is treated with the new multisite rTMS protocol consisting of high-frequency stimulation of the left dorsolateral prefrontal cortex (20 Hz, 1000 stimuli/day, which are applied in 20 trains with an intertrain interval of 25 seconds) followed by 1000 stimuli at 1 Hz over the left temporoparietal cortex and 1000 stimuli at 1 Hz over the right temporoparietal cortex. The stimulation parameters have been chosen according to a pilot study
[21] with a slight modification with respect to the number of stimuli. A detailed explanation for the choice of protocol can be found in Lehner and colleagues
[21].

The single-site group is treated with a single-site rTMS protocol consisting of 3000 stimuli/day that are applied at 1 Hz over the temporoparietal cortex contralateral to the tinnitus percept
[26]. Based on former studies, the left hemisphere is treated in case of bilateral tinnitus (for example
[27]). Since the goal of this study is to demonstrate superiority of the multisite stimulation over the current standard approach (stimulation of the temporoparietal cortex), an active stimulation protocol was chosen for comparison instead of placebo stimulation.

All patients receive 10 treatment sessions on 10 consecutive working days. The total number of stimuli per session is identical for both treatment groups (3000 stimuli per session). rTMS is performed with an intensity of 110% of the resting motor threshold but never higher than 60% of the maximal stimulator output. The resting motor threshold is determined at the beginning of the first treatment session and is defined as the minimal intensity at which at least five of 10 motor evoked potentials are 50 μV in amplitude in the right abductor digiti minimi. rTMS treatment is performed with a Medtronic MagPro Option stimulator (Medtronic, Minneapolis, MN, USA) connected to a 70 mm figure-of-eight coil. The coil is held tangential to the scalp with the handle pointing upwards. The temporoparietal cortices are localized using the 10–20 System by placing the coil between the temporal (T3/T4) and the parietal (P3/P4) EEG electrode sites
[28,29]. The dorsolateral prefrontal cortex is targeted by centering the coil 6 cm anterior from the part of the motor cortex that had been used for defining the resting motor threshold.

rTMS treatment is applied by nonblinded study staff not involved in any other study-specific procedures. Patient management and assessment, functional MRI and EEG measurements and the statistical analyses are done by psychologists and physicians who are blinded with respect to treatment conditions.

#### Outcome measures

The primary outcome measures are the change in the TQ score from baseline to end of treatment (interaction effect time × group) as well as the number of treatment responders as defined by a reduction in the tinnitus questionnaire score of ≥5 points at the end of treatment. Secondary outcome measures are changes in all scales and questionnaires (TQ, THI, numeric rating scales, Major Depression Inventory, World Health Organization Quality of Life assessment, hyperacusis questionnaire) between baseline and end of treatment as well as between baseline and all follow-up periods. Furthermore, the number of treatment responders at all follow-up time points is examined.

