**Methods/design:**

This is a randomized, double-blind, parallel-group study. Patients receive rTMS treatment on 10 consecutive working days using either the multisite rTMS protocol (left dorsolateral prefrontal, 1,000 stimuli, 20 Hz; left temporoparietal, 1,000 stimuli, 1 Hz; right temporoparietal stimulation, 1,000 stimuli, 1 Hz) or a single-site protocol (unilateral stimulation of the temporoparietal cortex, 3,000 stimuli, 1 Hz). Individuals aged 18 to 70 years with chronic tinnitus ≥6-month duration and a Tinnitus Handicap Inventory score ≥38 are recruited for the study. A total of 50 patients are needed to detect a clinical relevant change of tinnitus severity (α = 0.05; 1 – β = 0.80). Primary outcome measures are the change in the Tinnitus Questionnaire score from baseline to the end of treatment as well as the number of treatment responders as defined by a reduction in the Tinnitus Questionnaire score of ≥5 points. Furthermore, changes in brain structure and activity are assessed using (functional) magnetic resonance imaging and electroencephalography in the resting state. Those measurements are also performed in 25 healthy control subjects.

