### Objectives

Based on the findings in the pilot study, we hypothesize that the reduction of the Tinnitus Questionnaire (TQ) score as well as the number of treatment responders after 10 days of rTMS treatment and after follow-up periods of 3 and 6 months are higher when patients are treated using the new multisite stimulation protocol in comparison with single-site stimulation of the temporoparietal cortex. Treatment response is defined as an improvement of ≥5 points in the TQ score
[22]. Further aims of the study are as follows: to compare multisite stimulation with single-site stimulation with respect to a change of tinnitus severity as measured by the TQ, the Tinnitus Handicap Inventory (THI) and numeric rating scales assessing the loudness and annoyance of the tinnitus percept (baseline vs. end of treatment and all follow-up visits); to compare single-site stimulation with multisite stimulation with respect to a change in secondary outcomes such as quality of life, hyperacusis and depressive symptoms (baseline vs. end of treatment and all follow-up visits); to replicate and expand findings concerning the neural correlates of tinnitus using resting state EEG, MRI and resting-state functional MRI; to examine whether successful treatment with rTMS is correlated with changes in brain structure and activity; to examine whether treatment with multisite rTMS induces different brain changes than treatment with single-site rTMS (we assume that network alterations associated with tinnitus can be influenced more effectively using multisite stimulation as compared with single-site rTMS); and to determine whether brain structure and activity as measured by EEG and functional MRI at baseline are predictive for treatment response.

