#### Determination of sample size

The study is designed to find an interaction effect between group (single-site vs. multisite) and time (baseline, end of treatment). Based on our pilot data
[21] a small effect size of *f* = 0.1 for this interaction effect is assumed. Although small, such an effect is still an important step in tinnitus management. If the study sample size is determined to provide sufficient power (0.8) for detection of such an effect in a repeated-measures analysis of variance (with α = 0.05), a total of 42 tinnitus patients have to be examined. Due to the complex and time-consuming study design, a higher patient dropout rate than usual is assumed. A total of 50 patients (25 per group) are therefore planned to be included in the study.

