#### Statistical analysis

Missing data entries are handled with the last observation carried forward method. For the comparison of treatment responders in both groups, a chi-square statistic is calculated. For all secondary outcomes, an analysis of variance is used with the between-subjects factor group (multisite rTMS vs. single-site rTMS) and the repeated-measures factor time (baseline vs. end of treatment vs. all follow-up time points). EEG and (functional) MRI data are analyzed with MatLab-based analytic software (MathWorks, Natick, MA, USA; EEGLAB; FieldTrip; SPM). For both EEG and functional MRI data, different exploratory analyses focusing predominantly on connectivity measures will be done. As it is hypothesized to find altered connectivity patterns in tinnitus patients, imaging/EEG data of both patient groups are compared with data for the control group (baseline measurements of the tinnitus groups vs. single measurement of the controls). Furthermore, longitudinal analyses will be performed to test for a change of the connectivity patterns from before to after rTMS treatment (contrast: pre rTMS vs. post rTMS). Correlations of imaging data and questionnaire scores are used to identify potential predictors for rTMS outcome. As the present protocol has a clinical focus, we do not go into detail concerning the EEG and functional MRI analyses at this point.

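### Two co-equal primary outcomes share one alpha of 0.05 and one power calculation, with no rule for success: if either suffices the error rate exceeds 5%, and if both are required power falls below 0.80

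*Protocol article*

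**What the plan says.** - **Outcome measures** names two primaries. The first: "The primary outcome measures are the change in the TQ score from baseline to end of treatment", specified as the time × group interaction. The second, joined to it without ranking: "the number of treatment responders as defined by a reduction in the tinnitus questionnaire score of ≥5 points", at end of treatment. The abstract repeats the pair.
- **Objectives** puts both into one hypothesis: "the reduction of the Tinnitus Questionnaire (TQ) score as well as the number of treatment responders after 10 days of rTMS treatment" are expected to be higher with multisite stimulation. It does not say whether one or both must be significant.
- **Determination of sample size** covers the first only: "The study is designed to find an interaction effect between group (single-site vs. multisite) and time (baseline, end of treatment"). It uses f = 0.1, alpha 0.05 and power 0.8, giving 42 patients, raised to 50 (25 per group) for dropout. No responder rates or responder power are given.
- **Statistical analysis** gives the second its own test: "For the comparison of treatment responders in both groups, a chi-square statistic is calculated". No alpha level or continuity correction is attached.
- **Outcome measures** also lists TQ change between baseline and end of treatment among the secondary outcomes, so one contrast is both primary and secondary.

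**The concern.** The second primary is the first one cut at 5 points, so the same change score is tested twice. The article does not rank the tests, split alpha between them or require both. The stated alpha and power therefore describe one test, while a positive trial could rest on two.

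The possible rules have different consequences. If either result counts, the false-positive rate is above 0.05. If both must succeed, power is below 0.80. If one is significant and the other is not, the article does not say whether superiority, its stated goal, has been shown.

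**Working it through.** **Inputs from the article.** f = 0.1, alpha = 0.05, power = 0.80, N = 42 evaluable (21 per arm), 50 enrolled (25 per arm), responder cut at 5 points, chi-square for responders.

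**Inputs assumed, because the article gives none.** Pre-post correlation rho, control response rate (10–50%), normal change scores.

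**Step 1: reproduce N = 42.** For a group × time interaction with two groups and m = 2 time points, the noncentrality is λ = N·m·f²/(1 − rho), with df (1, N − 2).

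- rho = 0.90: λ = 42 × 2 × 0.01 / 0.10 = 8.4, power 0.807. The smallest N is 42.
- rho = 0.80: N = 82. rho = 0.50: N = 200.
- At 50 patients and rho = 0.90: λ = 50 × 2 × 0.01 / 0.10 = 10, power 0.87.

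So 42 follows if rho is about 0.90. The article does not state rho.

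**Step 2: put the planning effect on the change scale.** The 2 × 2 interaction F test equals a two-sample t test on change, for which λ = N·d²/4. Hence d² = 4 × 8.4 / 42 = 0.80 and d = 0.894.

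**Step 3: error rate with no true difference.** Simulated trials, 200,000 per setting: t test on change, chi-square on the same scores dichotomised, each at 0.05. For reference, two independent tests would give 1 − 0.95² = 9.75%, and the Bonferroni ceiling is 10%.

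| Success rule | 21 per arm | 25 per arm |
|---|---|---|
| Either, uncorrected chi-square | 7.4–8.6% | 8.2–8.9% |
| Either, continuity-corrected | 5.2–6.2% | 5.3–6.6% |
| Both, uncorrected | about 1–2.2% | about 1.1–2.6% |

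**Step 4: power at d = 0.894, control response 10–50%, uncorrected chi-square.**

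| | 21 per arm | 25 per arm |
|---|---|---|
| TQ change | 81% | 87% |
| Responders | about 52–61% | 60–74% |
| Both significant | about 49–59% | 58–72% |
| Exactly one significant | about 24–34% | about 17–31% |

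The last row is the power for at least one minus the power for both. With 30% control response at 25 per arm it is 89.2 − 72.1 = 17.1%. With 10% at 21 per arm it is 83.0 − 49.7 = 33.3%; repeat runs vary by a few tenths of a point.

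**Step 5: size of the uncorrected chi-square alone (exact enumeration).** At 25 per arm: 4.9%, 5.5%, 5.4%, 6.0% and 6.5% at response rates of 10, 20, 30, 40 and 50%. At 21 per arm it is 5.0% at 40% response and 4.6% at 50%.

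**Step 6: alternatives.** A fixed order (TQ change at 0.05, then responders) holds the familywise error at 5% and leaves N at 42. Splitting alpha to 0.025 each needs 52 evaluable patients for the TQ test at rho = 0.90; its power is 71% at 42 and 80% at 50.

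**The case against.** A reader might infer that the trial's alpha simply is 7–9%. The article does not support that. It never says that either outcome suffices, and the hypothesis in Objectives expects both to favour multisite. If both are required, the error is well below 5%. The inflation and the loss of power belong to opposite rules and must not be added together. The 7–9% also depends on an uncorrected chi-square, and the article does not name the variant.

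A reader might also infer that the chi-square is itself too liberal. That holds, by 1.0 to 1.5 points, at 25 per arm with 40–50% response. At 21 per arm and the same response rates its size is about 5% or just under.

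The power figures rest on rho = 0.90, which was found by working back from N = 42 and is not an input that the article states. Control response rates and normality are assumed too.

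Finally, this is a condensed article, and testing order is often left to an analysis plan. That would answer a complaint about missing detail. It does not answer this one: the article itself fixes two unranked primaries, one alpha, and one power calculation that covers only one of them. A responder definition also has a clinical use, and nothing here argues against reporting it.

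**Conclusion.** The point holds conditionally. The article's alpha of 0.05 and power of 0.80 do not both hold for a trial with two primary outcomes, whichever rule was meant:

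- **Either suffices:** false-positive rate about 7–9% with an uncorrected chi-square, about 5–6.6% with a continuity correction.
- **Both required:** no inflation, but joint power about 49–59% at 21 per arm and 58–72% at 25 per arm.
- **Under the planning effect,** the two primaries disagree in roughly 17–34% of trials, and the article does not say how such a result is to be read.

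The two-primary structure and the unpowered responder test are read directly from the text. The error rates assume normal change scores and a range of response rates. The power and disagreement figures also need rho = 0.90. The chi-square's own excess size is a minor side issue.

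**What to change.** Before unblinding:

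1. Name TQ change from baseline to end of treatment (time × group) as the sole primary outcome, at two-sided 0.05. It is the outcome that the trial is sized for.
2. Make end-of-treatment responders the key secondary outcome, tested formally only if the primary is significant. Report the risk difference with its confidence interval.
3. Delete TQ change from baseline to end of treatment from the secondary list; the follow-up changes stay.

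This restores 5% and leaves N at 42 evaluable. Replacing the chi-square with an exact unconditional test is optional.

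The cost is a documented amendment to a registered trial that has been recruiting since July 2012, and the loss of a second unadjusted chance at a positive primary result. No visit, measurement or sample size changes. The article says that the analysts are blinded, so the amendment can be made without knowledge of results by arm.

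### The primary TQ comparison is an unadjusted change-score test; adjusting for baseline TQ would be slightly more efficient and protect against chance imbalance, at negligible cost

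*Protocol article*

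**What the plan says.** Under Outcome measures, the first primary outcome is "the change in the TQ score from baseline to end of treatment (interaction effect time × group". The second is the number of responders, compared by chi-square under Statistical analysis.

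The section Determination of sample size rests on the same test: "The study is designed to find an interaction effect between group (single-site vs. multisite) and time (baseline, end of treatment". It states "a small effect size of *f* = 0.1 for this interaction effect is assumed", to be tested in a "repeated-measures analysis of variance (with α = 0.05", and concludes that "a total of 42 tinnitus patients have to be examined", raised to 50 (25 per group) for dropout. No correlation between baseline and end-of-treatment TQ is given.

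Under Statistical analysis, "For all secondary outcomes, an analysis of variance is used with the between-subjects factor group" and a repeated time factor that takes in baseline, end of treatment and every follow-up. Baseline TQ is collected, but no section uses it as a covariate. Randomization describes one balanced list with the whole sample as a single block, and no stratification.

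**The concern.** A time × group interaction with two levels of each factor has one numerator degree of freedom, and its F statistic is the square of the t statistic for the group difference in change. The change score fixes the slope of end-of-treatment TQ on baseline TQ at 1. With equal variances at the two times, the slope that minimises variance is the correlation rho, which is below 1. Two things follow.

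- Some precision is given up in a small trial.
- If the arms differ in baseline TQ by chance, regression to the mean carries a fraction (1 − rho) of that difference into the estimated effect.

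A related point concerns the secondary scales. The Objectives ask whether multisite stimulation gives a larger TQ reduction at the end of treatment and at 3 and 6 months. Outcome measures defines the secondary outcomes as changes from baseline to end of treatment and to the follow-ups. An omnibus group × time test over all visits has several numerator degrees of freedom and no direction. With baseline, end of treatment and two follow-ups it has (2 − 1)(4 − 1) = 3. A significant result does not by itself show superiority at any given visit.

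**Working it through.** **Inputs from the protocol article.** f = 0.1, alpha = 0.05, power 0.80, two groups, m = 2 time points, N = 42 evaluable and 50 planned (25 per arm). **Assumed, not in the document:** rho, the baseline/post correlation, with equal SDs at the two times.

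**1. The target on the TQ scale.** In a 2 × 2 interaction, f = 0.1 means cell effects of ±0.1 SD, so the difference in mean change is 4 × 0.1 = 0.4 SD.

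**2. Reproducing the stated N.** The noncentrality is lambda = f²·N·m/(1 − rho), with 1 and N − 2 degrees of freedom.
- At rho = 0.9: lambda = 0.01 × 42 × 2/0.1 = 8.4 and power is 80.7%. N = 42 is the smallest even total that reaches 80%.
- At rho = 0.8, 0.7 and 0.5 the required totals are 82, 120 and 200.
- At rho = 0.89 and 0.91 they are 46 and 38.

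So 42 implies rho of about 0.9.

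**3. Effect of adjustment.** Var(change) is proportional to 2(1 − rho) and Var(ANCOVA) to 1 − rho². The ratio is (1 + rho)/2, which is 0.95 at rho 0.9, 0.85 at 0.7 and 0.75 at 0.5. For ANCOVA power, lambda is multiplied by 2/(1 + rho) and by (N − 4)/(N − 3), the average penalty for chance covariate imbalance, with N − 3 residual degrees of freedom. At N = 42 and rho 0.9, lambda = 8.4 × (2/1.9) × (38/39) = 8.6 and power is 81.7%.

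| rho | N = 42: change → ANCOVA | N = 50: change → ANCOVA | Required N: change → ANCOVA |
|---|---|---|---|
| 0.95 | 97.9% → 97.9% | 99.2% → 99.2% | 22 → 24 |
| 0.9 | 80.7% → 81.7% | 87.3% → 88.2% | 42 → 42 |
| 0.8 | 51.6% → 54.8% | 59.1% → 62.7% | 82 → 74 |
| 0.7 | 37.2% → 41.6% | 43.2% → 48.4% | 120 → 104 |
| 0.5 | 24.4% → 30.2% | 28.3% → 35.3% | 200 → 152 |

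Simulation at rho 0.9 (10,000 trials per setting) agrees: 80.8% and 81.5% at N = 42, 87.3% and 88.3% at N = 50.

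**4. Chance imbalance with 25 per arm.** The SE of the baseline difference is sqrt(2/25) = 0.283 SD. The probability that it exceeds 0.3 SD in either direction is P(|Z| > 0.3/0.283) = 29%. A 0.3 SD difference shifts the change-score estimate by 0.3 × (1 − rho):
- rho 0.9: 0.03 SD
- rho 0.7: 0.09 SD
- rho 0.5: 0.15 SD

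These compare with a target of 0.4 SD.

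**The case against.** The strongest reply is that nothing here is stated wrongly. The interaction test matches the stated outcome (change) and the sample-size model, and over repeated randomisation it is valid and unbiased. That stands. A reader might infer that the planned estimate is biased, but the documents do not support this: the shift in step 4 is conditional on a particular imbalanced draw.

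A reader might also infer a substantial loss of power, or that adjustment would allow a smaller trial. At the correlation that the stated N implies, the gain is about 1 point and the required N stays at 42. The larger gains need a rho of 0.5 to 0.8. The document does not give such a value, and its own sample size does not fit one. If rho were that low, power with 50 patients would be 28% to 59% unadjusted and 35% to 63% adjusted. The main weakness would then be the unstated correlation, which ANCOVA does not repair.

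Nor is adjustment free. It costs a degree of freedom and a small penalty, and at rho 0.95 nothing is gained. It removes the linear effect of imbalance on the estimate, not the imbalance itself.

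A condensed article may leave per-visit contrasts to an analysis plan that is not shown, so the secondary-outcome point is a refinement rather than an error. Finally, a reader might extend the argument to the responder comparison. There is no support for that here, and a logistic model would replace the marginal comparison with a conditional odds ratio.

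What remains is that the article does fix the primary TQ test as an unadjusted one, although a better use of data already collected is available.

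**Conclusion.** The point holds as a modest improvement: the primary TQ test is valid but not the most efficient choice, and it is more exposed to chance baseline imbalance than it need be. At the implied rho of about 0.9 the gain is about 1 power point, and a 0.3 SD imbalance shifts the estimate by only 0.03 SD. At assumed correlations of 0.8, 0.7 and 0.5 the gain with 50 patients is 3.6, 5.2 and 7.0 points, and the shift reaches 0.15 SD at rho 0.5. Adjustment is therefore a cheap hedge against an unknown correlation, not a rescue. The figures rest on f = 0.1 for a two-time-point interaction, equal SDs at the two times and a linear baseline relation.

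**What to change.** Prespecify the primary TQ analysis as ANCOVA of end-of-treatment TQ on group, with baseline TQ as covariate, and report the adjusted mean difference with its 95% CI. For the secondary scales, report the same baseline-adjusted group contrast at each visit, with that scale's own baseline as covariate, in place of reliance on the omnibus group × time test. State the correlation assumed in the sample-size calculation. Leave the chi-square comparison of responders as it is.

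The cost is a change of wording, one degree of freedom and a small imbalance penalty. No new data are needed for the primary analysis, since baseline TQ is already collected.
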